### Experimental design and protocol description

A randomised parallel group design will be used for this trial (registration number: ISRCTN18311163). Participants will be randomly allocated by a third party to experience either:A fixed energy surplus via 7 days of overfeeding (+50%) and residual physical activity (≤4000 steps day^−1^) (SUR)

OR2.A matched energy surplus and residual physical activity (≤4000 steps day^−1^) with a daily 45-min bout of vigorous-intensity arm crank ergometry (SUR + ARM)

OR3.A matched energy surplus and residual physical activity (≤4000 steps day^−1^) with a daily 45-min bout of moderate-intensity treadmill walking (SUR + MOD)

OR4.A matched energy surplus with the addition of intermittent short bouts of walking during waking hours equivalent to the energy that would be expended by each participant during exercise if they had been allocated to the SUR + MOD group with an additional allowance of 4000 steps day^−1^ to account for permissible residual physical activity as in the other groups (SUR + BREAKS)

#### SUR group

In the SUR group, participants will restrict their daily physical activity to ≤4000 steps per day with no structured exercise allowed and will be required to over-consume their habitual diet by 50%.

#### SUR + ARM group

In the SUR + ARM group, participants will also restrict their daily physical activity to ≤4000 steps per day with no structured exercise allowed except a daily 45-min bout of arm crank ergometry at 70% V̇O_2peak_. Importantly, the SUR + ARM group will be prescribed additional energy intake to account for the energy expended during the exercise (i.e. habitual energy intake will be increased by 50% + energy expended during the exercise in order to standardise energy surplus; Table 1 and Fig. 1). The first exercise bout in the SUR + ARM group will be supervised, and compliance to the following six exercise bouts will be confirmed by combined heart rate/accelerometry (Actiheart, Cambridge Neurotechnology Ltd., Cambridge, UK) by reviewing each participant’s physical activity records after they have completed the study. The final exercise bout prescribed under the SUR + ARM treatment will be performed at a standardised time of day specific to each participant. This will take place at the same time as the exercise bout each individual had performed the day before baseline measures were taken and before 1400 h (i.e. to facilitate meaningful comparisons between baseline and follow-up).

**Table 1 Tab1:** Intervention arms employed in the study protocol

Intervention	Description
SUR	Overfeeding (50%) and restricted physical activity (≤4000 steps day^−1^)
SUR + ARM	Overfeeding (50% + energy expended during exercise) and restricted physical activity (≤4000 steps day^−1^) with a daily bout of vigorous-intensity arm crank ergometry (45 -min at 70% V̇O_2peak_)
SUR + MOD	Overfeeding (50% + energy expended during exercise) and restricted physical activity (≤4000 steps day^−1^) with a daily bout of moderate-intensity treadmill walking (45 -min at 50% V̇O_2max_)
SUR + BREAKS	Overfeeding (50% + energy expended during walking bouts) with addition of intermittent short bouts of walking during waking hours equivalent to the energy that would be expended by each participant during exercise if they had been allocated to the SUR + MOD group with an additional allowance of 4000 steps day^−1^to account for permissible residual physical activity in the other groups

**Fig. 1 Fig1:**
[figure not shown]
Schematic representation of the planned energy surplus that will be induced by the overfeeding and restricted physical activity models. The energy surpluses will be matched between all groups. CHO carbohydrates, PRO protein, EtOH alcohol, RMR resting metabolic rate, DIT diet-induced thermogenesis, PAEE physical activity energy expenditure

#### SUR + MOD group

In the SUR + MOD group, participants will also restrict their daily physical activity to ≤4000 steps per day with no structured exercise allowed except a daily 45-min bout of treadmill walking at 50% maximal oxygen uptake (V̇O_2max_). Importantly, the SUR + MOD group will be prescribed additional energy intake to account for the energy expended during the exercise (i.e. habitual energy intake will be increased by 50% + energy expended during the exercise in order to standardise energy surplus; Table 1 and Fig. 1). The first exercise bout in the SUR + MOD group will also be supervised, and compliance during the intervention will also be confirmed by combined heart rate/accelerometry records (Actiheart, Cambridge Neurotechnology Ltd., Cambridge, UK). The final exercise bout prescribed under the SUR + MOD treatment will be performed at a standardised time of day specific to each participant as in the SUR + ARM group.

#### SUR + BREAKS group

In the SUR + BREAKS group, participants will be asked to perform small bouts of walking throughout the day to reach their individual target steps with no structured exercise allowed. The daily target steps will be calculated from the data collected during the self-selected speed test and target steps calculation procedure. The energy expended during the walking bouts will be equivalent to the energy expended if each participant had been allocated to the SUR + MOD group, with an additional allowance of 4000 steps each day to account for permissible residual physical activity as in the other groups (i.e. the other groups will be allowed to do up to 4000 steps a day). Importantly, the SUR + BREAKS group will be prescribed additional energy intake to account for the energy expended during walking (i.e. habitual energy intake will be increased by 50% + energy expended during the walking bouts in order to standardise energy surplus; Table 1 and Fig. 1). Compliance to the walking bouts in the SUR + BREAKS group will also be confirmed by combined heart rate/accelerometry records (Actiheart, Cambridge Neurotechnology Ltd., Cambridge, UK). Participants will be advised to walk “little and often” throughout the day (i.e. approximately every 30–40 min), each bout lasting ~5 min (approximately 500–600 steps). In addition, participants will be asked to limit longer walks of greater than 1500 steps to only once per day, and to try and not exceed a maximum of 2000 steps in a single bout. Participants will also be instructed not to sit for longer than 1 h at a time.

### Calculations of energy surplus

The excess post-exercise oxygen consumption (EPOC) associated with each exercise bout will be estimated as 8.5%, 5.2% and 5% of energy expended during the exercise for the SUR + ARM [24], SUR + MOD [25] and SUR + BREAKS [25] groups, respectively. The diet-induced thermogenesis (DIT) associated with the extra food prescribed to all three intervention groups (compared to the SUR group) will be calculated as 10% of the energy expended during the bout of exercise (including EPOC [26]). The estimated EPOC and DIT associated with the exercise bout will then be added to the prescribed energy intake. Finally, the contribution of resting metabolic rate (RMR) towards total energy expenditure during each exercise session (45 min or equivalent for the SUR + BREAKS group) will be subtracted from the overfeeding calculation as this will have been already taken into account when prescribing the 50% overfeed based on a 24-h RMR.

### Preliminary assessments

#### Diet and physical activity assessments

Over a period of seven consecutive days, participants will record their habitual food and fluid intake prior to taking part in the study using a set of digital weighing scales (Model 3001, Salter, Kent, UK). Dietary records will be analysed using the Nutrition Analysis Software version 1.8 (Nutritics, UK), which is based on a food database in the UK. Energy intake will be estimated using this software, and DIT will be estimated pre-intervention as 10% of energy intake [26]. During this period, a combined heart rate/accelerometer monitor (Actiheart, Cambridge Neurotechnology Ltd., Cambridge, UK) will be used to determine habitual physical activity thermogenesis at baseline. A pedometer (3D TriSport, China) will be worn to record habitual daily step count.

#### Pre-trial fitness tests

In order to avoid unnecessary participant burden, maximum oxygen uptake will be assessed on the treadmill *and* on the arm crank ergometer for participants in the SUR group, but participants in the three exercise groups will only be required to have their relevant maximum oxygen uptake and other tests assessed (either on the treadmill or on the cycle ergometer).

##### Treadmill V̇O_2max_

Running maximal oxygen uptake (V̇O_2max_) tests will be performed by participants from the SUR, SUR + MOD and SUR + BREAKS groups at least 1 week prior to the first main trial. Participants’ V̇O_2max_ will be assessed on a treadmill prior to the intervention (ELG70, Woodway, Weiss, Germany) following a method adapted from Taylor et al. [27]. The percentage of O_2_ and CO_2_ in expired air samples for all tests will be determined using paramagnetic and infrared gas analysers, respectively (Series 1400, Servomex Ltd., Sussex, UK), calibrated according to the manufacturer’s instructions prior to use.

##### Arm crank V̇O_2peak_

Peak oxygen uptake (V̇O_2_ peak) will be determined for participants from the SUR and SUR + ARM groups using a continuous, progressive intensity test on an electrically braked arm crank ergometer (Lode Angio, Groningen, Netherlands). A cadence of 75 rpm will be encouraged throughout, and a starting intensity will be selected based on the participant’s ability. The resistance will be increased by 14 W every 3 min until the point of volitional exhaustion (approximately 9–12 min).

##### Gradient walking test

A gradient walking test will be performed by participants from the SUR + MOD and SUR + BREAKS groups to determine their 50% V̇O_2max_. The gradient walking test will be undertaken on a treadmill (ELG70, Woodway, Weiss, Germany) maintained at 6 to 7 km h^−1^ with an initial 2.5% gradient that will be increased by 2.5% every 5 min until the gradient reached 10%. To determine energy expenditure, expired air samples will be collected for 1 min at the end of each 5-min stage.

##### Self-selected speed test and target steps calculation

Participants randomised in the SUR + BREAKS group will perform a 15-min walking test at a self-selected speed to estimate the number of steps achieved in that time. Participants will be allowed 1 min to choose their “normal walking speed” whilst blinded from the treadmill speedometer. Once the speed has been selected, participants will walk at the chosen speed for the remaining 14 min, and expired air will be collected for 1 min at 5-min intervals to determine energy expenditure [28] and the total number of steps will be recorded during that time. The number of steps required to expend the equivalent energy as a 45-min walking bout at 50% V̇O_2max_ will be determined for each participant. Participants will then be assigned a specific number of steps to complete each day of the intervention period to match the energy expended during exercise if they had been allocated to the SUR + MOD group. This will be achieved by intermittent short bouts of walking during waking hours in the SUR + BREAKS group instead of a single bout for the SUR + MOD group and an additional allowance of 4000 steps day^−1^ to account for permissible residual physical activity as in the other groups. To monitor this, pedometers will be worn each day during the intervention period to record the total step count. Pedometers will be worn by all other groups to measure adherence to the permitted 4000 steps day^−1^.

### Main trial day protocol

The same experimental procedures will be completed on both baseline and follow-up trial days. During 3 days leading up to the intervention week, volunteers will be asked to adhere to their habitual lifestyle (i.e. diet and physical activity/exercise), and all participants will be asked to perform a 30-min bout of running the day before starting the intervention before 1400 h at their usual running pace. This will ensure that the last bout of exercise will have been standardised for all participants. On the morning of the baseline trial (Fig. 2), participants will report to the laboratory at 0700 ± 0.5 h following an overnight fast (≥10 h). Twenty-four hours prior to each main laboratory trial day, participants will abstain from caffeine (tea/coffee) and alcohol. The SPIRIT figure showing the respective time points for assessments and intervention is provided in Fig. 3 (see Additional file 1).

**Fig. 2 Fig2:**
[figure not shown]
Overview of trial outline, including all measurements and sampling that will take place

**Fig. 3 Fig3:**
[figure not shown]
SPIRIT figure showing an overview of the assessment schedule at baseline and follow-up in the study. DEXA dual-energy X-ray absorptiometry

### Body composition analysis

Body mass will be assessed to the nearest 0.1 kg using digital scales (TANITA Corp., Tokyo, Japan) with participants wearing identical light clothing at baseline and follow-up. Waist and hip circumference will be measured using a non-stretch tape to the nearest 0.1 cm, based on World Health Organization guidelines [29]. Body composition will be assessed by dual-energy X-ray absorptiometry (DEXA; Discovery, Hologic, Bedford, UK) to determine muscle mass and fat mass. All measurements will be made following a quality control scan of a spine phantom with known properties in accordance with the manufacturer’s instructions.

### Resting metabolic rate measurement

Participants will then rest in bed for 10 min, after which resting metabolic rate (RMR) will be determined via indirect calorimetry based on four 5-min expired gas collections with concurrent measurement of inspired air composition; a reliance of standard atmospheric concentrations has recently been discouraged [30]. RMR will be accepted as stable within 100 kcal day^−1^ [31, 32], and the lowest of these measures will be accepted as RMR [20].

### Blood sampling

Following RMR assessments, a 20-G cannula (BD Venflon™ Pro, Becton, Dickinson & Co., Sweden) will be inserted into an antecubital vein from which baseline 20 mL of blood will be drawn through two 10-mL syringes and placed into serum separation beads and EDTA-containing tubes (Sarstedt Ltd, Leicester, UK). Plasma samples will be centrifuged immediately at 3466*g* at 4 °C for 10 min (Heraeus Biofuge Primo R, Kendro Laboratory Products Plc., Tyne and Wear, UK). Serum samples will be left to clot for 15 min at room temperature before centrifugation. All samples will be dispensed into 0.5-mL aliquots and immediately cooled on dry ice and then stored at −80 °C. A small aliquot of EDTA blood will be used to obtain the full leucocyte differential and other haematological variables (SF-300, Sysmex Ltd., Milton Keynes, UK).

### Adipose tissue biopsy and processing

Adipose tissue samples (~0.5 g) will be taken under local anaesthetic (1% lidocaine) from the area around the waist approximately 5 cm lateral to the umbilicus using a 14-G needle using an aspiration technique with follow-up biopsies sampled from the opposite side [20]. The sample will be cleaned with isotonic saline, and any clot will be manually removed. After weighing the sample, it will be homogenised in 5 mL of TRIzol (Invitrogen, UK) and placed on dry ice before being stored at −80 °C.

### Muscle biopsy and processing

After the baseline blood sample and adipose tissue biopsy, a muscle biopsy will then be collected from the vastus lateralis. Participants will rest in a supine position whilst a 3–5-mm skin incision will be made under local anaesthetic (1% lidocaine) using a surgical blade. The percutaneous needle biopsy technique [33] will then be used to obtain between 30 and 100 mg of wet muscle tissue from this site. At follow-up, a muscle biopsy will be taken from each participant’s opposite leg and the use of dominant/non-dominant limbs will be counterbalanced. Muscle samples will be immediately placed in a ventilated Eppendorf tube and snap-frozen in liquid nitrogen where they will be stored during the trial before being stored at −80 °C.

### Oral glucose tolerance test

After the baseline blood sample, adipose tissue and muscle biopsies, participants will consume 113 mL of Polycal (Nutricia Advanced Medical Nutrition, Trowbridge, UK) and 87 mL of water, equivalent to 75 g of anhydrous glucose, within 5 min. Further 5-mL blood samples will be drawn at 15-min intervals for the next 2 h. The intravenous cannula is to be kept patent through periodic flushing with 0.9% NaCl (B. Braun, Sheffield, UK) infusion, with the first 5 mL of each blood drawn being discarded. Blood pressure will also be measured three times during the final 15 min of the oral glucose tolerance test (OGTT) using an automated blood pressure monitor (Boso Medicus Prestige, Bosch + Sohn GmbH, Jungingen, Germany), and the average will be reported.

## Discussion

Our previous work showed that short-term overfeeding combined with reduced physical activity induces a state of insulin resistance, hyperinsulinaemia and altered expression of several key genes within adipose tissue [20]. Importantly, the addition of daily vigorous-intensity running mostly prevented these changes independent of any net effect on energy imbalance [20]. The three exercise models in the present study will enable us to compare the benefits of different physical activity/exercise approaches in the context of increased caloric intake and reduced physical activity. Specifically, the comparison of the SUR + ARM group versus the SUR group will help us establish whether vigorous upper-body exercise has the ability to prevent negative changes in metabolic function induced by short-term overfeeding and reduced physical activity, which may be relevant to wheelchair users. Furthermore, the SUR + MOD and SUR + BREAKS groups will allow us to determine whether moderate-intensity exercise has a similar impact on metabolic health as vigorous-intensity running and whether the same benefits can be gained from distributing that amount of exercise throughout the day. These alternative forms of exercise may be more appropriate for or preferred by specific populations. This study will provide a novel insight regarding the potential of different forms of daily exercise at preserving metabolic function at the whole-body level as well as within adipose tissue and skeletal muscle in the face of a standardised energy surplus. Our analysis will focus on genes and proteins known to be significantly impacted by a week of overfeeding and/or reduced physical activity within both tissues. This approach will help elucidate the mechanisms by which exercise benefits physiological function and human health even in the face of a considerable energy surplus.

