## Methods/design

### Participants

To address these objectives, a cohort of 48 healthy young men who satisfy the inclusion and exclusion criteria outlined below will be recruited via advertisement from the local community. Written consent will be obtained from all participants after the initial meeting, and participants will be informed that they can withdraw from the study at any time without consequence. Eligibility will be assessed by a series of self-report questionnaires. Eligible participants will then be randomly allocated to one of four parallel intervention arms using a stratified randomisation scheme. The randomisation schedule will be generated by a senior author ([name]) using an electronic random number generator and concealed from those involved in participant management ([name]) to prevent biased allocation [21, 22]. Participant assignment will be requested via email, and full details of the overall randomisation scheme will be published once all allocations are completed to prevent deciphering. This will feature a factor for objectively measured physical activity level (PAL) and body mass to ensure an even distribution of less active (PAL: <1.75) and more active (PAL: ≥1.75) as well as lighter (<77 kg) and heavier (≥77 kg) participants in each treatment arm, respectively. The ensuing protocol for this study has received ethical approval from the National Health Service Research Ethics Committee (reference: 15/SW/0014).

Inclusion:Male.Aged 18–40 years old.Active (exercise more than 30 min per day, at least three times per week).Stable body mass for at least 6 months (<3% increase or decrease [23]).Able and willing to comply with study procedures.Have the capacity to provide informed consent.

Exclusion:Female.Currently smoking.Aged less than 18 years or greater than 40 years.Positive response to one or several questions from the Physical Activity Readiness Questionnaire (PAR-Q).Taking any medication that might interfere with the study outcomes (This will be reviewed by the research team on a case-by-case basis should a potential participant be on regular medication. The British National Formulary will be checked for potential effects that might introduce bias in the study.).Illness/condition that might interact with study measures (e.g. diabetes, heart disease) or pose undue personal risk.

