### Power calculation

We plan to recruit 48 young (18–40 years), healthy, weight-stable, active men from the local population. Using data from our previous study [20], it was estimated that a sample size of 12 in each treatment group will provide approximately 90% power to detect a difference in ∆ insulin iAUC of 17 ± 16 versus 1 ± 6 nmol 120 min L^−1^ using an independent *t* test at an alpha level of 0.05. Recruitment will proceed on a rolling basis until the adequate sample size is reached; emphasis will be placed on considering the demands of the study before enrolling to reduce loss to follow-up.

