### Statistical analysis

All data from participants having successfully completed the study will be included in the analysis. The statistical analysis plan is for a primary comparison between intervention groups and control arm. The precise time-course of responses within and between trials will be analysed using factorial two- and three-way mixed-model analysis of variance (group × day and group × day × time, respectively). For all the above statistical approaches, statistical significance will be set at an alpha level of *p* ≤ 0.05. We will explore the use of confidence intervals and magnitude-based inferences to assess the clinical significance of the effect.

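### The Discussion promises a verdict on moderate exercise against vigorous running, but no running arm is randomised; its question of equal benefit from distributed walking needs a direct MOD–BREAKS estimate, which 12 per arm gives only coarsely

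*Protocol article*

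**What the plan says.** All references are to the protocol article.

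- **Discussion.** It says the SUR + MOD and SUR + BREAKS groups will make it possible to "determine whether moderate-intensity exercise has a similar impact on metabolic health as vigorous-intensity running and whether the same benefits can be gained from distributing" the same amount of exercise over the day. The running result is attributed there to the investigators' previous study (reference 20).
- **Participants; Experimental design and protocol description; Table 1.** "Eligible participants will then be randomly allocated to one of four parallel intervention arms using a stratified randomisation scheme". The arms are SUR, SUR + ARM, SUR + MOD and SUR + BREAKS. None has running as its intervention. The 30-minute run in Main trial day protocol is done by every participant on the day before the intervention starts, as a standardisation step.
- **Background, objectives.** There are three, each asking whether one exercise form can prevent the adverse metabolic changes. None names running, and none names MOD against BREAKS.
- **Statistical analysis.** "The statistical analysis plan is for a primary comparison between intervention groups and control arm". Mixed-model ANOVA with group × day and group × day × time terms is also planned. Confidence intervals and magnitude-based inferences are to be explored.
- **Power calculation.** Twelve per group "will provide approximately 90% power to detect a difference in" change in insulin iAUC of 17 ± 16 versus 1 ± 6 nmol 120 min/L, by an independent t test at alpha 0.05.

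**The concern.** The Discussion sentence sets two questions that go beyond the objectives, and they differ in kind.

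The first is MOD against vigorous running. No participant in this trial is randomised to running, so any answer sets MOD results from this trial beside running results from an earlier one. Differences in participants, period and procedures are then mixed with the effect of exercise type. No analysis plan, seen or unseen, can supply a concurrent running arm.

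The second is MOD against BREAKS. The arms for it exist, but it asks about sameness, while the stated comparison and the sample size concern a difference from SUR. Two separate results against SUR do not show that MOD and BREAKS are alike, and neither does a non-significant difference between them. At stake is a possible published conclusion that short walking breaks are as good as one continuous bout, when the data may be compatible with losing much of the benefit.

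**Working it through.** **Inputs.** From Power calculation: n = 12 per arm; planning difference 17 − 1 = 16; SDs 16 and 6; alpha 0.05. Sidedness is not stated, so two-sided is assumed. The section does not say which earlier group each value belongs to; the power figure does not depend on it. The SD in MOD and BREAKS is not given, so I assume a common SD and use the range 6 to 16, with the root-mean-square planning value in between.

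**1. The plan's own figure.**
- SD = √((16² + 6²)/2) = √146 = 12.08.
- SE = 12.08 × √(2/12) = 4.93.
- Normal approximation: 16/4.93 − 1.96 = 3.24 − 1.96 = 1.28, giving power 90.0%. The stated figure reproduces.
- The exact two-sided t test gives 87.3%, and a simulated unequal-variance (Welch) test 85.3%.

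This is power to detect a 16-unit difference. It says nothing about showing similarity.

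**2. MOD against running.** There are no randomised running participants, so there is no within-trial contrast and nothing to compute.

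**3. Precision of MOD minus BREAKS.** Half-width of the 95% CI = t(0.975, 22 df) × SD × √(2/12), with t = 2.074 and √(2/12) = 0.408.

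| Assumed SD | Half-width | As % of 16 | Power to detect an 8-unit difference |
|---|---|---|---|
| 6 | ±5.1 | 32% | 88% |
| 12.08 | ±10.2 | 64% | 34% |
| 16 | ±13.5 | 85% | 22% |

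The last column uses the noncentral t distribution, two-sided 0.05. Eight units is half the planning difference and is illustrative only; the article gives no margin. At SD 12.08 a true loss of that size would be non-significant about two times in three.

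**4. Chance of supporting equal benefit if it is true.** Suppose the true difference is zero and the test is whether the 95% CI excludes an 8-unit loss. By symmetry the chances are those in the last column: about 88%, 34% and 22%. For 80% power by the normal approximation, n per arm = 2 × (SD × (1.96 + 0.84)/8)²:
- SD 6: 9 per arm.
- SD 12.08: 36 per arm.
- SD 16: 63 per arm.

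A two-sided equivalence test (5% per side) at SD 12.08 with 12 per arm has about 5% power for a margin of ±8, 52% for ±12 and 87% for ±16. The last margin equals the whole planning effect.

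**The case against.** The strongest reply has five parts.

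- **The sentence poses a question.** A reader might infer that the plan predicts MOD and BREAKS will match running. It does not; it says the groups will allow the investigators to determine whether they do. This stands. The fault is in the word determine, since the design cannot settle the running question.
- **The article states no rule for declaring similarity.** A reader might infer that two significant results against SUR, or a non-significant MOD–BREAKS difference, will be read as sameness. Nothing says so, and exploring confidence intervals points the other way. This stands; the point here is to close off that reading.
- **MOD against BREAKS is answerable.** Both arms are randomised, the BREAKS step target is built to match MOD energy expenditure, and the group × day ANOVA can yield the contrast. A primary comparison with control does not exclude others. This stands, so this part concerns precision and interpretation.
- **A margin or planned contrast may be in the full protocol or SAP.** This stands, and its absence from the article is not held against the plan.
- **The precision depends on the SD.** At SD 6 the contrast is reasonably informative. If breaking up the exercise lost the whole benefit and the planning values applied, power would be about 85% to 90%. This also stands; partial loss with a larger SD is the weak case.

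The article does credit the running result to previous work, so a careful reader would know its source. It still does not say that the comparison would be non-randomised.

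**Conclusion.** The point holds in two parts of unequal strength.

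**Running.** The design cannot determine whether moderate exercise has a similar impact to vigorous running. Any such statement is an indirect comparison with the previous study. This rests on the list of arms alone and needs no assumption.

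**Distribution over the day.** The design permits the MOD–BREAKS contrast, so it would be wrong to say that the question cannot be addressed. However, "a primary comparison between intervention groups and control arm" is the only primary comparison stated, and 12 per arm was chosen for a 16-unit difference. At the root-mean-square planning SD, an observed difference of zero would leave a 95% CI of about −10 to +10, which does not exclude losing half the 16-unit effect. At SD 6 it would be about −5 to +5, which does. These figures assume a common SD in both arms, 12 completers each and roughly normal changes.

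The three objectives, each addressed by comparison with SUR, are untouched.

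**What to change.** 1. In the Discussion, delete the running clause, or state that any comparison with running is indirect, non-randomised and made against the previous study.
2. Report MOD minus BREAKS in change in insulin iAUC directly, as an estimate with a 95% CI, beside the comparisons with SUR. If the full plan already contains this contrast, refer to it.
3. State that equal benefit will not be inferred from both arms beating SUR or from a non-significant difference. It will be claimed only if the CI excludes a loss that the sponsor has justified in advance; otherwise the result will be called inconclusive. The 8 units used above only illustrate the arithmetic and are not a proposed margin.

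The cost is some rewording and one contrast from data already to be collected, with no added participants or measurements. The downside is a more modest claim: unless the SD proves to be near the low end of the range, the MOD–BREAKS result may well be inconclusive.
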